## Abstract

**Background:**

Young people are vulnerable to experiencing problematic levels of loneliness which can lead to poor mental health outcomes. Loneliness is a malleable treatment target and preliminary evidence has shown that it can be addressed with digital platforms. Peer Tree is a strength-based digital smartphone application aimed at reducing loneliness. The study aim is to reduce loneliness and assess the acceptability, usability, and feasibility of Peer Tree in young people enrolled at university.

**Methods:**

This will be a pilot randomised controlled trial (RCT) comparing a strength-based digital smartphone application (Peer Tree) with a control condition. Forty-two young people enrolled at university will be recruited for this pilot RCT. Participants with suicidal ideation or behaviours, acute psychiatric symptoms in the past month, or a current diagnosis of a mood or social anxiety disorder will be excluded. Allocation will be made on a 1:1 ratio and will occur after the initial baseline assessment. Assessments are completed at baseline, at post-intervention, and at follow-up. Participants in the control condition complete the same three assessment sessions. The primary outcome of the study will be loneliness. Depression, social anxiety, quality of life, acceptability, usability, feasibility, and safety of Peer Tree will also be measured as secondary outcomes.

**Discussion:**

This trial will report the findings of implementing Peer Tree, a smartphone application aimed at reducing loneliness in university students. Findings from this trial will highlight the initial efficacy, acceptability, and feasibility of using digital positive psychology interventions to reduce subthreshold mental health concerns. Findings from this trial will also describe the safety of Peer Tree as a digital tool. Results will contribute evidence for positive psychology interventions to address mental ill-health.

**Trial registration:**

Australian New Zealand Clinical Trial Registry ACTRN12619000350123. Registered on 6 March 2020

**Supplementary Information:**

The online version contains supplementary material available at 10.1186/s13063-022-07029-7.

## Administrative information

Note: the numbers in curly brackets in this protocol refer to SPIRIT checklist item numbers. The order of the items has been modified to group similar items (see http://www.equator-network.org/reporting-guidelines/spirit-2013-statement-defining-standard-protocol-items-for-clinical-trials/).

## Background and rationale {6a}

Young people are vulnerable to experiencing high levels of loneliness. In Australia, 1 in 4 young people aged 18 to 25 years report problematic levels of loneliness [1, 2]. This is counterintuitive to common views of young people, given that young people are thought to be less socially isolated, often participating in school or work, and are competent users of digital technology [1]. While loneliness and social isolation are related, they are distinct concepts [3]. Loneliness is defined as a *subjective* experience of social isolation where there is a discrepancy between an individual’s desired and actual social relationships [4]. Loneliness may be more related to the quality of social relationships than to the quantity [5], and this may be more problematic for young people who may favour having a greater number of relationships over quality relationships [6].

Young adulthood is also known to be a period of transition and change. It is common for young adults to move out of home, separate themselves from established social networks and support systems, and be exposed to new social environments [7]. This is particularly true for young people at university; one key challenge in making a transition and adjusting to university is the formation of new peer groups [8]. Strong social bonds and reciprocal relationships with others have been found to be the strongest protective factor against loneliness in this population [9]. This is important as loneliness is an established risk factor for the development of mental ill-health in young people [1]. Therefore, addressing loneliness is a necessary step in improving the mental well-being of young people at university.

Young people have also been found to be particularly vulnerable to mental ill-health, with approximately 26% of those aged 16 to 24 experiencing mental health issues in Australia [10]. University students, compared with their non-university peers, report a higher prevalence of psychological distress with 19.2% of university students having very high levels of psychological distress (K10 score over 30), compared with 3% in the general population of the same age [11]. Higher levels of loneliness have been found to predict greater anxiety, stress, and depression in university students and increase the likelihood of dropping out from university [3, 12]. Thus, loneliness is an antecedent to poor mental health.

A key protective factor that reduces this risk is social connectedness and forming reciprocal bonds with peers [13–15]. While universities offer mental health and psychological support, young people are less likely to seek professional help [16], rather they rely on their peers for ‘informal’ mental health support [17, 18]. One way that young people rely on their peers is through digital technology. Therefore, the use of online mental health programmes could assist with engagement and compliance to treatments in this age bracket [17]. Previous research utilising online interventions to reduce various mental health symptoms has found positive results among both clinical (e.g. first-episode psychosis) and non-clinical samples of young people [19–22].

Fortunately, loneliness is feasible to address with online programmes [23–25]. In a recent trial, an 8-week Internet-based CBT intervention was administered to a community sample [26, 27]. Loneliness decreased significantly at the completion of the intervention as well as at the 2-year follow-up [26, 27]. Besides CBT, the majority of interventions targeting loneliness have used methods to improve social skills, enhance social support, and increase social contact [24]. Other digital interventions that hold the potential to address loneliness include those adopting strength-based, positive psychology interventions (PPIs). PPIs are designed to promote positive cognitions, feelings, and behaviours and improve overall psychological well-being [28]. More conventional psychological interventions target the amelioration of specific deficits (e.g. symptom reduction), but PPIs are designed to increase the sense of meaning and purpose in life and connectedness with others and enhance positive emotions [29–31]. A PPI targeting loneliness will build on participants’ social strengths and skills and will encourage the development of positive emotions within existing relationships by supporting users to show more prosocial behaviours towards others.

There is initial evidence in support of the efficacy of digital interventions for targeting loneliness in young people. In our previous pilot studies, we designed and developed +Connect, a PPI in the form of a smartphone application [32, 33]. Our pilot data supported the acceptability, feasibility, and safety of PPIs, as well as the potential for PPIs to reduce loneliness and mental health symptoms (i.e. social anxiety) in young people including with and without mental disorders [32, 33]. In a recent pilot RCT study, a smartphone application, Nod, employing a combination of positive psychology and cognitive and behavioural approaches, was used to address loneliness in university students [25]. Participants completed social challenges (e.g. acts of kindness, gratitude exercises) that were accompanied with written testimonials from young people over a 4-week period. Participants were also encouraged to provide reflections about their experiences in an attempt to restructure negative thoughts about social interactions. While initial data showed there were no significant effects in those reporting low depressive symptoms at baseline, Nod was found to be a safe and acceptable smartphone application that buffered the negative effects of loneliness in those who reported high levels of depression at baseline.

Recent evidence supports the need for interventions that target loneliness as a primary outcome rather than secondary to mental health [23]. Given that loneliness predicts subsequent deterioration in mental health outcomes, and current CBT models target mental health symptoms, it is important to address loneliness as a primary outcome. The study aim is therefore to reduce loneliness and improve mental health outcomes in vulnerable university students.

## Objectives {7}

The objective of this study is to evaluate the acceptability, feasibility, safety, and initial efficacy of a positive psychology smartphone application intervention called Peer Tree. Peer Tree is a digital smartphone intervention targeting loneliness and is a new iteration of our previous application +Connect. Peer Tree includes many features from +Connect [30, 31] but also includes the personalisation of modules based on user symptom profiles, a peer- and clinician-moderated chat forum, and animated videos to address loneliness in young people using a positive psychology framework.

It is hypothesised that Peer Tree participants, compared with the control participants, will report significantly lower loneliness at post-intervention, and these effects will remain at follow-up. It is also anticipated that Peer Tree participants, compared with control participants, will report significantly lower social anxiety and depressive symptoms, and higher quality of life and well-being outcomes at post-intervention as well as at follow-up.

## Methods

### Trial design {8}

Peer Tree is a pilot randomised controlled trial utilising a parallel groups design where participants are randomly allocated to either the Peer Tree intervention or control (i.e. No Peer Tree) group. There will be no blinding in this trial for assessors. Once determined to be eligible during the baseline assessment, participants will be randomised to one of the two conditions. Participants in both groups will complete a post-intervention assessment 6 weeks after the baseline or once they have finished the intervention. Participants in the Peer Tree arm will be given a maximum of 8 weeks to complete the smartphone application, after which they will complete the post-intervention assessment. Participants will then complete a follow-up assessment 3 months after the post-intervention assessment. Figure 1 displays the Consolidated Standards of Reporting Trials (CONSORT) flow diagram of the study procedure. The protocol was designed in accordance with the Standard Protocol Items: Recommendations for Interventional Trials (SPIRIT) and Good Clinical Practice Guidelines.

**Fig. 1 Fig1:**
[figure not shown]
CONSORT flow diagram for the Peer Tree randomised controlled trial

### Study setting {9}

This trial will be conducted at Swinburne University of Technology. Assessment sessions will be conducted in person at Swinburne University or online using a secure video conference service.

### Eligibility criteria {10}

Participants meeting the following criteria will be eligible for the study: (1) enrolled in any programme at an Australian university, (2) aged between 18 and 25 years, (3) English is their primary language, and (4) own a smartphone. Exclusion criteria are as follows: (1) self-reports acute psychiatric symptoms in the past month where the participant’s mental state has been worse than is usual for them (e.g. debilitating mood and anxiety symptoms), (2) reports any suicidal ideation or behaviour, (3) reports risk of harm to others or risk of damage to objects or property, (4) reports psychiatric hospitalisation in the past month, and (5) reports current diagnosis of a mood disorder or social anxiety disorder.

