### Recruitment {15}

Recruitment will take place from three main channels: (1) flyers posted around university campuses, (2) social media posts with links to the study will be posted on university-affiliated pages and through paid Facebook and YouTube adverts, and (3) through emails to list of students who access different services at the sponsor university.

Students who express interest in the study will be contacted by a member of the research team for an initial phone screen to provide more detailed information about the study and assess eligibility for the baseline assessment. The phone screen comprises of a standardised set of questions that assesses the interested student’s suicide ideation or behaviour risk, risk of harm to others and property, and mental health status (i.e. the presence of acute psychiatric symptoms in the past month) to ensure they are suitable for the baseline assessment. The phone screen will not guarantee eligibility and potential participants are informed of this at the outset. If the participant is still interested and deemed eligible at the end of the phone screen, a time is scheduled for the baseline assessment, during which eligibility is confirmed through a more comprehensive assessment.

Participants are reimbursed with a $50 e-Gift card for their time attending each of the three assessment sessions. If during the baseline assessment a student is found to be ineligible, they are reimbursed for their time with a $15 e-Gift card.

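### Entry does not depend on loneliness, so the loneliness comparison should adjust for baseline UCLA-LS3 and the conclusion should be confined to students unselected for loneliness

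*Protocol article*

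**What the plan says.** The Background section of the protocol article states the aim: "The study aim is therefore to reduce loneliness and improve mental health outcomes in vulnerable university students". The Discussion paragraph of the Abstract expects findings on subthreshold mental health problems.

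Eligibility criteria {10} asks that participants be "enrolled in any programme at an Australian university, (2) aged between 18 and 25 years, (3) English is their primary language" and own a smartphone. Among the exclusions is anyone who "reports current diagnosis of a mood disorder or social anxiety disorder" or who "self-reports acute psychiatric symptoms in the past month", the latter qualified as a mental state worse than is usual for that person.

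The phone screen in Recruitment {15} covers "suicide ideation or behaviour risk, risk of harm to others and property, and mental health status". Sequence generation {16a} confirms eligibility with the mood and social anxiety modules of the SCID-5-RV and then allocates in blocks. UCLA-LS3 is measured at all three visits (Table 1), but no score is used for entry, and no stratification by it is described.

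Statistical methods {20a} asks whether loneliness changes more over time under Peer Tree. For the mixed-model analysis of variance it names baseline, post-intervention and follow-up as the three levels of the repeated factor. The intention-to-treat mixed model is put to the same question without its terms being spelled out.

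**The concern.** The Background reports that "1 in 4 young people aged 18 to 25 years report problematic levels of loneliness". It also describes a similar student app trial with "no significant effects in those reporting low depressive symptoms at baseline". A sample taken without regard to loneliness, and without diagnosed mood or social anxiety disorder, may include people whose scores have limited room to fall.

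Two things are at stake. First, when baseline scores are widely spread, how the analysis uses them matters a good deal at 21 per arm. Second, a conclusion worded for people with subthreshold problems would describe a group that the entry criteria do not select.

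**Working it through.** **1. Is loneliness used anywhere before allocation?** The inclusion criteria cover enrolment, age, language and smartphone. The phone screen covers risk and mental health status. The baseline check covers SCID-5-RV mood and social anxiety modules and risk. None uses a loneliness score.

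**2. How many participants would have problematic loneliness?** With 42 participants allocated 1:1:
- share 25% (the protocol's population figure): 42 × 0.25 = 10.5, or 5.25 per arm
- share 50% (assumed): 21
- share 75% (assumed): 31.5

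The protocol does not say which applies to its volunteers.

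**3. The planned sample size.** Alpha, the numerical effect size and the correlation are not stated, so 42 cannot be tied to one set of inputs. It can be reached. For a group-by-time F test with f = 0.20, m = 3 visits, r = 0.5 and two-sided alpha 0.05 (all but the three visits assumed):
- λ = f²·N·m/(1 − r) = 0.04 × 42 × 3 / 0.5 = 10.08, with 2 and 80 degrees of freedom, giving power 0.803.

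The figure is not shown to be wrong.

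**4. Three-level test against baseline adjustment.** Assumptions: 21 per arm, SD 1 at each visit, equal correlation r between visits, no expected arm difference at baseline (randomisation), a difference of 0.6 SD at both later visits, two-sided alpha 0.05, complete data.

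*Group by time, three levels.* The arm differences 0, 0.6 and 0.6 have mean 0.4. Squared deviations are 0.16 + 0.04 + 0.04 = 0.24. λ = (21/2) × 0.24/(1 − r).
- r = 0.5: λ = 5.04, power 49%
- r = 0.7: λ = 8.40, power 72%

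*Mean of the two later scores, adjusted for baseline.* Residual variance = (1 + r)/2 − r². SE = √(2/21 × residual variance), with 39 degrees of freedom.
- r = 0.5: variance 0.50, SE 0.218, 0.6/SE = 2.75, power 76%
- r = 0.7: variance 0.36, SE 0.185, 0.6/SE = 3.24, power 88%

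*Where the gain comes from.* A single contrast of the later mean minus baseline, without a covariate, has variance (1 + r)/2 + 1 − 2r = 0.75 or 0.45 and power 59% or 81%. At r = 0.5, about 10 points come from asking one focused question and about 17 from using baseline as a covariate. At r = 0.7 it is about 8 and 8.

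**5. Could an arm-by-baseline interaction find who benefits?** I simulated a 0.5 SD effect in the loneliest quarter only and none elsewhere, with 21 per arm and continuous baseline UCLA-LS3. Power is about 9% at r = 0.5 and 10% at r = 0.7.

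**The case against.** The best defence is that aim and eligibility agree. The Background and Discussion call young people and students in general vulnerable, so vulnerable students can simply mean students. Provisions for post-trial care {30} says that the population is not clinical, so excluding diagnosed disorders is deliberate. The exclusion for acute symptoms, illustrated by debilitating mood and anxiety symptoms, leaves room for milder ones. All of this stands, and for that reason the point is not about whom the trial enrols.

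A reader might infer more than the document supports:

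- *Many participants start at the floor.* No UCLA-LS3, SIAS or CES-D distribution is given, and lacking problematic loneliness is not the same as scoring near the minimum of a 20-item scale.
- *Power collapses.* If only a share of the sample could respond and the rest had exactly zero effect, power in the setting of step 3 would fall from 80% to 54%, 27% and 10% at shares of 75%, 50% and 25%. Zero effect in the rest is pure assumption, and 25% is a population figure applied to volunteers for a loneliness app.
- *The cited app trial shows that non-lonely students do not benefit.* Its results were split by depressive symptoms, not loneliness.
- *Chance imbalance spoils the comparison.* At a 25% share, fewer than 5 lonely students in a given arm has probability 37%, but 6 or more has 43%, which is ordinary variation. A gap of 5 or more between arms has about 11%. The planned test already compares change from baseline.

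**Conclusion.** The point holds in a limited form. Nothing in the criteria selects for loneliness or subthreshold symptoms. Baseline UCLA-LS3 is likely to carry useful information that the three-level test uses inefficiently, and the Abstract's conclusion reaches beyond the sample.

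Under the assumptions of step 4, adjusting for baseline raises power from about 49% to 76% at r = 0.5 and from about 72% to 88% at r = 0.7. The size rests on an assumed 0.6 SD effect that is equal at both later visits and on equal correlations. The gain from a single averaged contrast would shrink if the effect faded by follow-up. The hypothesis that it persists makes the average a fair target.

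It would go too far to say that a null result could not be interpreted. Baseline UCLA-LS3 is collected, its distribution can be shown, and the trial is a pilot of initial efficacy alongside acceptability, feasibility and safety.

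**What to change.** 1. In Statistical methods {20a}, compare the arms on post-intervention and follow-up UCLA-LS3 with baseline UCLA-LS3 as a covariate, in place of the three-level group-by-time test. A mixed model with arm, visit, arm by visit and baseline gives the difference at each later visit and their average.
2. Report the baseline UCLA-LS3 distribution by arm. In the Abstract and the Discussion, confine the conclusion to students unselected for loneliness and without current mood or social anxiety disorder.
3. Label any look at arm by baseline UCLA-LS3 as exploratory and state its very low power at 21 per arm.

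The cost is rewording and a narrower conclusion; the scores are already scheduled. A participant with no later score adds nothing to the adjusted comparison, so that number should be reported by arm. Trial status says that data collection is under way, so the change should be dated and made before outcomes are compared by arm.

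A minimum loneliness score at entry is not recommended. It would mix two populations partway through and slow recruitment.

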### Who will take informed consent? {26a}

During the initial assessment, a researcher will obtain verbal and written consent from the participant.

### Additional consent provisions for collection and use of participant data and biological specimens {26b}

During the baseline assessment, participants will have the option to allow their data to be used in future studies. This data will be aggregated to a group level, and no identifiable information will be used in any future studies.

## Interventions

### Explanation for the choice of comparators {6b}

As our focus is the examine the effectiveness of the intervention above and beyond an individual’s usual activities, we selected a control group who did not receive the Peer Tree intervention and compared it to a group who received Peer Tree intervention.

### Intervention description {11a}

#### Features of the digital intervention

##### Modules

Peer Tree delivers a series of 42 psychoeducational modules in the form of videos, animations, and images over a 6–8-week period. Each module helps develop core skills for a particular topic. Peer Tree delivers a series of 42 psychoeducational modules in the form of videos, animations, and images over a 6–8-week period. Each module helps develop core skills for a particular topic. There are three types of videos that participants will watch: animation (narrated animation videos illustrating concepts), actor (actors role-playing concepts), and shared experience (young people with lived experience of loneliness discussing concepts). Each module takes approximately 2–6 min to complete, with new modules being released each day to the user only if they had completed the previous module.

##### Challenges

Participants will also be asked to participate in challenges. These are designed to help apply what participants learn within the application in real life. If participants choose to take on a challenge, they will have between 1 and 7 days to complete the challenge depending on the module. Once participants complete a challenge, for example, doing 5 acts of kindness per day, they will earn a token.

